## Methods/Design

### Trial Design

The study is a randomized controlled superiority trial with two parallel groups and primary endpoints of condom use self-efficacy, condom use intention, sexual and reproductive health knowledge, and delayed sexual initiation 9 months post-intervention. Block randomization will be performed with a 1:1 allocation.

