**Fig. 1 Fig1:**
[figure not shown]
SPIRIT Figure

All data collection will be administered via ACASI (Audio Computer Assisted Self-Interview) technology on a laptop or tablet, which includes an audio component for participants with literacy challenges. This method has been shown to decrease response bias in AI communities, especially around sensitive topics [25]. The youth baseline assessment will be administered during two pre-camp registration days prior to randomization; the parent-trusted adult baseline will be administered prior to camp at the time of consent. All youth and parent/trusted adult follow-up assessments will be delivered in participant’s homes, at school or another location of their choosing.

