#### Primary Outcome Measures

The primary outcome variables are sexual/reproductive health knowledge, sexual initiation, condom use self-efficacy and intent to use a condom at next sex as changed from baseline to post-intervention between intervention and control participants. These variables were chosen because they are applicable to all study participants.

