### Sample Size Calculation and Statistical Analysis

Our goal is to recruit 567 youth (and their parent/trusted adult) balanced within two age groups (11–12, 13–15 and 16–19), for a total of 1134 participants (567 youth and 567 parents/trusted adults). We expect a maximum attrition rate of 25%, based on past rates in similar evaluations [18, 19, 29, 30].

Sample size estimates were based on the variables of condom use self-efficacy and sexual initiation because these confirmatory research questions apply to all study participants, and prior studies have shown them to be associated with reductions in risky sexual behavior, teen pregnancy and STI incidence [23]. We hypothesize that the RCL intervention will increase condom use self-efficacy in the intervention group compared to the control group and that the intervention group will have a lower proportion of participants who initiate sex, compared to controls, at study end line.

The condom use self-efficacy scale ranges from 1–5. Our pilot trial [18] provided data on the condom use self-efficacy score among the control group (mean = 2.6, SD = 1.0), degree of intra-team correlation (“k” = 0.12) and potential loss to follow-up over 9 months (20% average reduction in team size, i.e., from 9 down to 7.2 youths). Although this trial will utilize individual randomization, the intervention will be carried out with teams of 8–12 participants each, which will require accounting for intra-team correlation.

We will use the average of two follow-up measures of condom use self-efficacy per participant (intra-measure correlation = 0.7) to reduce error in outcome measurement [31]. To achieve 90% power to detect a theoretically meaningful between-group difference of 0.47 points on this scale over 9 months post-intervention, ~32 teams per study arm will be required. Thus, we will enroll and randomize a total of *n* = 284 participants per study arm (32 teams/arm *9 participants/team), for a total sample size of *n* = 567 participants. We have reduced the significance level used in sample size calculations to 0.0125 to account for multiplicity corrections during analyses. This same sample size will be sufficient to detect a 19.7% between-group difference, with 80% power and 0.0125 significance level, in the percent of participants who report ever having had sex. This estimate is conservative based on our past retention rates and accounts for up to 25% loss to follow-up, while adjusting for the intra-team correlation.

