This sample size will also be able to detect meaningful differences between the intervention and control groups with at least 80% power, given the assumptions listed above: 6.7% between-group difference in reproductive/sexual health knowledge score [estimating a mean score (SD) of 76% (16%) in the control group] and 20.5% between-group difference in intention to use a condom at next sex (estimating 55% in the control group).

Study hypotheses will be initially tested under an “intent-to-treat” model in which data are analyzed according to randomization assignment. We will then conduct “completer analyses” on those subjects finishing at least two-thirds of the 9 intervention sessions. Intervention impact will be evaluated by comparing primary study outcomes between intervention and control groups across the three time points: baseline, 3 and 9 months post-intervention. Initially, summary scores of outcomes will be stratified by participation in the intervention versus control groups and by time point and compared using chi-square tests (for binary or categorical outcomes), t-tests and analysis of variance (for continuous outcomes). The equivalence of the two study groups at baseline will be compared across a range of background variables. Generalized linear mixed effects models (GLMMs) accounting for within-group correlation across longitudinal data will then be applied.

Outcomes will be modeled as a function of group assignment and time since intervention. The association between outcomes and time will be explored visually using scatterplots and lowess smoothers. Restricted cubic splines will be added to reflect deviations from linearity. GLMM with random intercepts for peer group and study participant will be used to account for the hierarchical structure of the data: peer group, participants nested within peer group and assessments nested within study participants. If siblings enter the study together during the same wave, they will be randomized to the same study group (intervention or control) to limit contamination. In this case, analyses will be adjusted to take into account intra-sibling correlation as well. Missing data will be handled as follows: (1) document reason(s) for missing data to inform model development; (2) assess treatment dropouts to do intent-to-treat analysis; (3) conduct sensitivity analysis to compare inferences that are based on different plausible reasons for missingness [32, 33].

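### The mixed model names only group and time over baseline, 3 and 9 months; with no stated interaction, baseline adjustment or contrast, a literal fit dilutes the effect

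*Protocol article*

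**What the plan says.** All of this is in the protocol article.

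- **Sample Size Calculation and Statistical Analysis** describes the comparison as "comparing primary study outcomes between intervention and control groups across the three time points: baseline, 3 and 9 months post-intervention". The model sentence is "Outcomes will be modeled as a function of group assignment and time since intervention". On the shape of time it adds "Restricted cubic splines will be added to reflect deviations from linearity", and on clustering "GLMM with random intercepts for peer group and study participant will be used to account for the hierarchical structure of the data". No group-by-time term, baseline covariate, baseline constraint or tested contrast is named.
- **Primary Outcome Measures** defines the outcomes "as changed from baseline to post-intervention between intervention and control participants".
- **Trial Design** places the primary endpoints at 9 months; its list ends with "delayed sexual initiation 9 months post-intervention".
- **The sample size text** takes the mean of the two follow-up measures as the powered quantity: "To achieve 90% power to detect a theoretically meaningful between-group difference of 0.47 points on this scale over 9 months post-intervention".
- **Data Collection Time Points** (text after Figure 1) fixes when baseline is taken: "The youth baseline assessment will be administered during two pre-camp registration days prior to randomization".

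**The concern.** The youth baseline precedes randomisation, so the expected difference between arms at baseline is zero. If baseline is an outcome row and the model has only a group term and a time term, the group coefficient is an average of the arm difference over all three visits, including that zero. It is then not the change from baseline, not the 9-month difference, and not the two-follow-up average on which the trial was sized.

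The spline sentence suggests that baseline is indeed an outcome row. Two scheduled follow-ups alone cannot show a departure from a straight line, apart from scatter in visit dates or the later visits that depend on further funding.

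At stake are a diluted estimate and a loss of power against the stated 90%.

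**Working it through.** **Inputs from the sample size text:** control mean 2.6, SD 1.0, k = 0.12, correlation between measures 0.7, difference 0.47, significance level 0.0125 (taken as two-sided, z = 2.498), 32 teams per arm, and 9 youths per team falling to 7.2 (20% loss) or 6.75 (25% loss).

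**1. The plan's own figure.** Averaging two measures multiplies the variance by (1 + 0.7)/2 = 0.85. Reading k as a between-cluster coefficient of variation (Hayes-Bennett formula), with intervention mean 2.6 + 0.47 = 3.07:

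teams = 1 + (2.498 + 1.282)² × [2 × 0.85/7.2 + 0.12² × (2.6² + 3.07²)] / 0.47² = 1 + 14.28 × 0.469/0.2209 = 31.3, rounded up to 32.

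The stated figure reproduces. Power with 32 teams is 90.7% at 7.2 youths and 89.6% at 6.75. If k is instead read as an intraclass correlation with the same 0.85 factor, 26.6 teams suffice at 7.2 youths. The meaning of k is therefore an assumption, and both readings are carried below.

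**2. What the literal model estimates.** For group and time main effects with a random participant intercept (peer-group intercept left out):

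- Complete data, equal effect d at 3 and 9 months: (0 + d + d)/3 = 0.667d, so 0.47 becomes 0.313.
- A fraction q of youths gives baseline only. A completer carries weight 3/(1 + 2 × 0.7) = 1.25 and a baseline-only youth carries 1, so the coefficient is (1 − q)(2d/2.4) / [(1 − q) × 1.25 + q]. For q = 0.20 this is 0.556d and for q = 0.25 it is 0.526d.
- Complete data, effect growing linearly (one third of its 9-month size at 3 months): (0 + 1/3 + 1)/3 = 0.444 of the 9-month effect.
- Complete data, effect only at 9 months: 0.333 of it.

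A 40-replicate simulation with 20% giving baseline only, fitted with a participant intercept, averaged 0.235 (0.50d). The standard deviation over replicates was 0.107, so the simulation error of the mean is 0.107/√40 = 0.017, and this is compatible with 0.556 × 0.47 = 0.261. Adding a group-by-post term returned 0.473.

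**3. Power of the literal group test** (equal effects of 0.47; retained youths have all three measures, whose mean has variance factor (1 + 2 × 0.7)/3 = 0.80):

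| Reading of k and team effect | Two-follow-up average | Literal group coefficient |
|---|---|---|
| Coefficient of variation | 90-91% | 53-55% |
| Intraclass correlation, design effect | 94-95% | 62-64% |
| Variance components, team effect at all visits | 92% | 57% |
| Variance components, team effect only after baseline | 92% | 76% |

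The last two rows use team 0.12, person 0.58, residual 0.30, and 32 × 6.75 = 216 youths per arm:

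- Literal coefficient, within-team variance 0.58 + 0.30/3 = 0.68: SE = √[2(0.12/32 + 0.68/216)] = 0.117, and 0.313/0.117 = 2.67 gives 57%.
- With the team effect absent at baseline, 0.12 is replaced by 0.12 × 4/9: SE = 0.098 and power 76%.
- Two-follow-up average, within-team variance 0.58 + 0.30/2 = 0.73: SE = 0.119 and power 92%.

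**4. If an interaction is intended.** Same components, team effect only after baseline, 9-month contrast:

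| Contrast | Within-team variance | SE | Power |
|---|---|---|---|
| 9 months alone | 0.88 | 0.125 | 89.6% |
| Change from baseline | 0.60 | 0.114 | 94.7% |
| Baseline-adjusted | 0.88 − 0.58²/0.88 = 0.498 | 0.110 | 96.2% |

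If the team effect is present at every visit it cancels from the change score, and power is near 100%.

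**The case against.** The strongest reply is that the article lists predictors and does not say main effects only. A longitudinal model for outcomes defined as change from baseline ordinarily carries a group-by-time term, and a condensed article may leave that term and the contrast to the analysis plan. Another reading also avoids dilution: if only the follow-up values, or changes from baseline, are modelled, an additive group term is the average follow-up difference, which is what the trial was sized on. This stands. A reader might infer that the trial will fit a main-effects model, but the document does not say so.

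A reader might also take one third as the shrinkage that the plan implies. It is not: it needs complete data, equal effects at both follow-ups and an additive scale. For condom intention on a logit scale it is only approximate.

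Under the interaction reading the remaining loss is small, 94.7% against 96.2%, and both exceed 90%. That stands too.

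Nor is the spline and lowess wording an error. With three scheduled visits a three-knot spline reproduces categorical visit, and a flexible time term is reasonable if the later visits are funded.

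What the reply does not remove is that the article describes the model in some detail (terms, time function, random intercepts), puts baseline among the compared points, and leaves unnamed the term that carries the treatment effect. If a spline-by-group interaction was meant, it has more than one coefficient, and the article does not say which combination is tested at 0.0125.

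**Conclusion.** The point holds as a conditional one. The named terms, taken literally, give a group coefficient that matches none of the three quantities the article sets out: change from baseline, the 9-month endpoint, or the two-follow-up average. Under that reading the estimate is at most about two thirds of the effect when the effects at 3 and 9 months are equal (0.31 instead of 0.47), and less under the planned attrition or a growing effect. Power for 0.47 points is then roughly 53-76%. That range rests on the assumed meaning of k, on when the team effect arises, on equal follow-up effects and on a two-sided 0.0125 level.

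A reader might infer a false-positive risk. There is none from this source, because the group test stays valid under the null. If an interaction is intended, only a slight loss of precision and an unnamed contrast remain.

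**What to change.** For condom use self-efficacy, knowledge and condom intention:

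1. Treat visit as categorical.
2. Model the 3- and 9-month values with the baseline value as covariate, or fit all three visits with the baseline means constrained equal between arms.
3. Include group-by-visit, and keep the random intercepts for peer group and participant.
4. Name one primary contrast, either the 9-month difference or the average of the two follow-ups, and use it consistently in Trial Design, Primary Outcome Measures and the sample size text.
5. If the 9-month difference is chosen, restate its power, because the trial was sized on the two-visit average.

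Dropping lowess and splines from the primary model is an optional simplification. Sexual initiation is outside this recommendation.

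The cost is wording, since the baseline is already collected. The one real trade-off is in step 4: making 9 months the sole contrast gives up the averaging on which the sample size relied.

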### Randomization

Participants will be individually randomized to receive the intervention or control program. Participants will be assigned to either program through a stratified block randomization sequence using Stata 14 [24] to ensure a 1:1 allocation of study conditions occurs within each gender and age sub-group (11–12, 13–15 and 16–19). Since both the RCL and control program include a youth-parent component, siblings will be randomized to the same group.

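### If the main test is the arm difference in change from baseline, the constant peer-group intercept drops out of it, and team correlation arising after baseline is left out of the standard error

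*Protocol article*

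**What the plan says.** All references are to the Protocol article.

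- **Model (Sample Size Calculation and Statistical Analysis).** The fixed part is given as "Outcomes will be modeled as a function of group assignment and time since intervention", and arms are compared "across the three time points: baseline, 3 and 9 months post-intervention". For clustering, "GLMM with random intercepts for peer group and study participant will be used to account for the hierarchical structure of the data". No team-by-time effect is named, and no group-by-time term is written out.
- **Outcome definition (Primary Outcome Measures, repeated in the Abstract).** The four primary outcomes are compared "as changed from baseline to post-intervention between intervention and control participants".
- **Timing of baseline (Data Collection Time Points).** "The youth baseline assessment will be administered during two pre-camp registration days prior to randomization".
- **Allocation (Randomization).** "Participants will be individually randomized to receive the intervention or control program". Siblings are kept together.
- **Why clustering matters (Sample Size Calculation and Statistical Analysis).** "the intervention will be carried out with teams of 8–12 participants each, which will require accounting for intra-team correlation".
- **Teams (Intervention).** Peer groups are same-sex and chosen by the youth themselves, and each is taught by two community health workers over eight days.

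**The concern.** The article gives team delivery as its reason for allowing for team correlation. Delivery comes after the youth baseline, so correlation that delivery creates is present at 3 and 9 months but not at baseline. A random intercept that takes one value per team across all visits cannot represent this. If the arm effect is read as a difference in change, the intercept is subtracted away and the model treats the participants' changes as independent, whatever team they were in.

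Ordinary differences between teams in how much they change would then be counted as evidence about the programme. Confidence intervals would be too narrow, and the 0.0125 level chosen for multiplicity would not be held. Writing in a group-by-time term does not help, because that term is where the understated standard error appears.

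**Working it through.** **1. The plan's own figure.** Inputs from the sample size section: control mean 2.6, SD 1.0, difference 0.47, power 90%, level 0.0125 (taken as two-sided), k = 0.12, follow-up correlation 0.7, team size 9 falling to 7.2. The multiplier is (2.498 + 1.282)² = 14.28.

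- k as a coefficient of variation, with two measures averaged (variance (1 + 0.7)/2 = 0.85): 1 + 14.28 × [2 × 0.85/7.2 + 0.12² × (2.6² + 3.07²)]/0.47² = 31.3, so 32 teams.
- k as an intra-class correlation (ICC), no averaging: 14.28 × 2 × (1 + 6.2 × 0.12)/7.2/0.47² = 31.3, so 32 teams.
- k as an ICC, with averaging: 0.85 × 31.3 = 26.6, so 27 teams.

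The stated figure of about 32 is reproduced. The sample size allows for team correlation and is not in question. The arithmetic does not settle which meaning k has.

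**2. Why the intercept cancels.** For participant i in team j, take the mean of the two follow-ups minus baseline. A team effect u_j common to all visits contributes u_j − u_j = 0. A team effect v_j present only at follow-up remains in full, and the stated model has no term for it.

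**3. Size for a continuous outcome.** Follow-up variance is 1 = 0.12 team + 0.58 participant + 0.30 residual, so the two follow-ups correlate 0.7. Let f be the share of the 0.12 that exists only after baseline; this is an assumption, varied from 0 to 1. Baseline variance is held at 1. There are 32 teams per arm with 7 followed in each, so 224 participants per arm.

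- True variance of an arm's mean change: 0.12f/32 + (0.45 + 0.12f)/224, where 0.45 = 1.5 × 0.30.
- Variance the random-intercept model assigns: (0.45 + 0.12f)/224.
- Ratio R = 1 + 7 × 0.12f/(0.45 + 0.12f).
- Type I error = 2[1 − Φ(z/√R)], with z = 2.498 at 0.0125 and 1.960 at 0.05.

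| Share f | R | Error at 0.0125: formula (simulated) | Error at 0.05: formula (simulated) |
|---|---|---|---|
| 0 | 1.00 | 0.0125 (0.013) | 0.050 (0.050) |
| 0.10 | 1.18 | 0.022 | 0.071 |
| 0.25 | 1.44 | 0.037 (0.039) | 0.102 (0.105) |
| 0.50 | 1.82 | 0.064 (0.064) | 0.147 (0.144) |
| 1 | 2.47 | 0.112 (0.114) | 0.213 (0.210) |

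Simulated values are from 20,000 trials per setting; f = 0.10 was done by formula only.

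**4. Sensitivity.**
- *k as a coefficient of variation.* The between-team SD is 0.12 × 2.6 = 0.312, so the ICC is about 0.097. At 0.0125 the formula gives 0.020, 0.032, 0.054 and 0.096 for f = 0.10, 0.25, 0.50 and 1.
- *Fitted models.* Three-level models were fitted by REML to 389 simulated trials with 9 enrolled per team, about 20% dropout and f = 1. The change contrast rejected in 15.7% at nominal 1.25% and 25.7% at nominal 5%. With a team effect added at follow-up the figures were 1.5% and 7.2% (simulation error about 0.6 and 1.1 points).
- *Additive group effect, same fitted models.* 1.8% and 6.9%; in balanced data 1.3% and 4.5%.

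**5. A test that lets teams differ in change.** A t-test on team mean changes (64 − 2 = 62 degrees of freedom) rejected in 1.2% to 1.3% at nominal 1.25% across the values of f. Its power for 0.47 points at f = 1: the standard error is √[2 × (0.12/32 + 0.57/224)] = 0.112, so 0.47/0.112 = 4.19 against a critical value of 2.57, about 94%. At f = 0.50 it is about 99%.

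**The case against.** The strongest reply is that the article never says the change contrast is the test. Its model sentence names group and time without an interaction. Trial Design places the endpoints at 9 months, and the sample size uses the average of two follow-up measures with no baseline subtracted. For a comparison of follow-up values, a peer-group random intercept is the right term. For an additive group effect over all three visits, the level is close to nominal. This stands, and it makes the finding conditional. It does not remove it: the additive effect averages in a visit made before randomisation, so it is not the change by which the primary outcomes are defined.

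Second, the post-baseline share is unknown. Self-selected, same-sex friends may already be alike, and the proficiency examination and fidelity monitoring should limit differences between facilitators. This also stands, and it is why a range is shown. At one tenth the error is less than twice nominal. Only a share of zero removes the problem, and that would mean team delivery creates no team differences, contrary to the article's reason for allowing for them.

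Third, sexual initiation and condom intention are powered as percentages. Under a logit link the cancellation is only approximate, and these outcomes were not simulated, so the table should not be applied to them.

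A reader might infer that the trial's main test will reject a true null several times too often. The documents do not support that without conditions, because they fix neither the tested contrast nor the share of team correlation that is new after baseline.

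**Conclusion.** The concern holds in conditional form. The stated random effects do not fit the stated outcome definition: if the arm difference in change from baseline is tested with them, team correlation arising after baseline is ignored and the standard error is too small.

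At nominal 0.0125, the true level for a continuous outcome runs from nominal, if none of the correlation is new, to about nine times nominal, if all of it is. At one quarter it is about three times. At nominal 0.05 the corresponding figures are about one, four and two times. The multiples are slightly lower if k is a coefficient of variation.

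These figures assume balanced data, 7 followed per team, normal outcomes and a two-sided test. In the zero-share row they also assume that baseline correlates with each follow-up as strongly as the follow-ups do with each other. The plan should be changed, because the contrast is left open and a model that is safe under any share costs little.

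**What to change.** In Sample Size Calculation and Statistical Analysis, state the arm contrast that is tested for each primary outcome, and replace the random-effects sentence with one of these:

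- **Baseline as covariate.** Model the 3- and 9-month outcomes with the baseline value as covariate, a peer-group random intercept and a participant random intercept.
- **Baseline as outcome.** Keep all three visits, with the participant intercept and a peer-group effect that can differ between baseline and follow-up (team-by-time, or a team effect added only after baseline).

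In either case, test the arm contrast on between-team degrees of freedom, about 62 with 32 teams per arm.

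The cost is a sentence or two of specification and no new data. Confidence intervals will be somewhat wider. The second form has one more variance component, which may be hard to estimate for the binary outcomes; there the baseline-adjusted form is simpler.

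### For the two continuous primary outcomes, the random-intercept model can understate the standard error of change from baseline, if baseline correlates less with follow-up than the two follow-ups do with each other

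*Protocol article*

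**What the plan says.** All references are to the Protocol article.

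- **Model.** Under 'Sample Size Calculation and Statistical Analysis', a "GLMM with random intercepts for peer group and study participant will be used to account for the hierarchical structure of the data". Assessments are nested in participants and participants in peer groups. The arms are compared over baseline, 3 and 9 months. Outcomes are modelled on group and time. The section names no random slope, freer visit covariance, robust standard error or group-by-time term. It does not say whether baseline enters as a response or a covariate.
- **Outcome definition.** Under 'Primary Outcome Measures' (and in the Abstract), the primary outcomes are taken "as changed from baseline to post-intervention between intervention and control participants". 'Trial Design' places the primary endpoints at 9 months.
- **Correlation.** The only within-person figure is that between the two follow-up measures of self-efficacy, "intra-measure correlation = 0.7".
- **Level.** "We have reduced the significance level used in sample size calculations to 0.0125 to account for multiplicity corrections during analyses".

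**The concern.** A participant random intercept with constant residual variance implies one correlation for all three visit pairs. The fitted value is close to the average of the three true ones. If the two pairs that involve baseline are less correlated than the follow-up pair, the average is too high for them. The variance of a change from baseline falls as that correlation rises, so the model would report too small a standard error for the quantity that defines the primary outcomes.

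There is reason to expect a weaker link at least between baseline and 9 months. Youth baseline is taken at registration before camp. The youth-parent lesson may come up to 3 months after camp, and follow-ups are counted from completion of the intervention. Baseline therefore lies roughly 9 to 12 months before the 9-month visit, while the two follow-ups are 6 months apart. Baseline is also collected in a different setting from the follow-ups.

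At stake are confidence intervals that are too narrow and a false-positive rate above the level planned for multiplicity, for two of the four primary outcomes. One of them, self-efficacy, set the number of teams.

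**Working it through.** **Inputs from the document.** Level 0.0125; sidedness is not stated, so two-sided is assumed and z = 2.498. Correlation between follow-ups r = 0.7. Control values "mean = 2.6, SD = 1.0"; "theoretically meaningful between-group difference of 0.47 points on this scale"; k = 0.12; team size 9 falling to 7.2; 90% power.

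**Assumed input.** Baseline-to-follow-up correlations r03 (3 months) and r09 (9 months); range shown below. Variances are set to 1 at each visit.

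**Step 1. The plan's own figure.** With k read as a between-team coefficient of variation and the variance of the mean of two follow-ups equal to (1 + 0.7)/2 = 0.85:

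teams per arm = 1 + (2.498 + 1.282)² × [2 × 0.85/7.2 + 0.12² × (2.6² + 3.07²)]/0.47² = 31.3.

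With 25% loss (team size 6.75) it is 32.4. The stated figure of about 32 is reproduced. This calculation uses follow-up values only, so it says nothing about the baseline correlation.

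**Step 2. Formulas.** Let rbar = (r03 + r09 + 0.7)/3.

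- 9 months minus baseline: true variance 2(1 − r09); model variance 2(1 − rbar).
- Mean of 3 and 9 months minus baseline: true variance 1.85 − r03 − r09; model variance 1.5(1 − rbar).
- Actual size = 2 × [1 − Φ(2.498 × √(model/true))].

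**Step 3. Equal baseline correlations (r03 = r09).**

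| r03 = r09 | 9 m: true / model | size | averaged: true / model | size |
|---|---|---|---|---|
| 0.3 | 1.40 / 1.133 | 2.5% | 1.25 / 0.85 | 3.9% |
| 0.4 | 1.20 / 1.00 | 2.3% | 1.05 / 0.75 | 3.5% |
| 0.5 | 1.00 / 0.867 | 2.0% | 0.85 / 0.65 | 2.9% |
| 0.6 | 0.80 / 0.733 | 1.7% | 0.65 / 0.55 | 2.2% |
| 0.7 | 0.60 / 0.60 | 1.25% | 0.45 / 0.45 | 1.25% |
| 0.75 | 0.50 / 0.533 | 1.0% | 0.35 / 0.40 | 0.8% |

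At 0.5 the standard error is too small by 7% for the 9-month contrast (√(0.867/1.00) = 0.931) and by 13% for the averaged contrast (√(0.65/0.85) = 0.874). REML fits to simulated null data, without team effects and with 20% lost after baseline, gave 4.2%, 3.7%, 2.8%, 1.8% and 1.3% for the averaged contrast at 0.3, 0.4, 0.5, 0.6 and 0.7.

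**Step 4. Plain decay with time.** Take correlation 0.7^(lag/6), lag in months, with baseline 3 to 6 months before the first follow-up.

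| lag to 3-month visit | r03, r09 | 9 m: true / model | size | averaged: true / model | size |
|---|---|---|---|---|---|
| 3 months | 0.837, 0.586 | 0.829 / 0.585 | 3.6% | 0.428 / 0.439 | 1.1% |
| 6 months | 0.70, 0.49 | 1.02 / 0.74 | 3.3% | 0.66 / 0.555 | 2.2% |

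**Step 5. Readings with no inflation.** A group main effect over all three visits keeps 1.25% at any baseline correlation, because compound symmetry with the average correlation gives the right variance for the mean of the three visits. With baseline as a covariate and only two follow-ups as responses, there is only one visit-pair correlation left to fit.

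**The case against.** A reader might infer that the planned tests will run at 2-4%. The document does not support that as a fact.

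- **The deciding correlation is not given.** If both baseline correlations are 0.7 there is no error, and above that the test is conservative. This stands, and the point is conditional on it.
- **The inflated test is not written down.** No group-by-time term is named, and a main effect of group keeps its size. This stands in part. A main effect over three visits averages in a baseline difference expected to be zero, so 0.47 shrinks to 0.47 × 2/3 = 0.31. That does not match the outcome definition, so it does not settle the matter.
- **The higher figures belong to the averaged contrast.** The primary endpoint is at 9 months, where equal baseline correlations of 0.6 to 0.3 give 1.7-2.5%. This stands. Under decay the order reverses: 3.3-3.6% at 9 months and 1.1-2.2% for the average.
- **Differing responses to the programme cannot be the reason.** If the programme changes nobody's score, there is no differing response. This stands as to that rationale, but decay with time needs no programme effect.
- **Scope.** It is also tempting to extend the figures to sexual initiation and condom intention. Those are binary, the common correlation holds only on a latent scale, and the figures do not carry over.
- **The 0.0125 level** is stated for the sample size; the multiplicity procedure for the analysis is not set out. Its use as the test level here is an inference.
- **A condensed article may leave covariance detail to an SAP.** That would excuse silence. Here the random-effects structure is stated, and a better one is available at almost no cost.

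**Conclusion.** The concern holds conditionally, for condom use self-efficacy and knowledge. The stated model imposes one within-person correlation on baseline, 3 and 9 months. The standard error of the change is understated for 9 months minus baseline when r09 is below the average of the three correlations. For the averaged contrast the condition is that the mean of r03 and r09 is below 0.7. A nominal two-sided 1.25% then becomes:

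- 9 months minus baseline: 1.7-2.5% (equal baseline correlations 0.6 to 0.3) or 3.3-3.6% (decay);
- mean of both follow-ups minus baseline: 2.2-3.9% or 1.1-2.2% respectively.

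This rests on four assumptions: a two-sided test, a group-by-time test with baseline as a response, equal variances at the visits, and baseline correlations that the document does not report. It concerns participant-level correlation only; clustering by team is a separate question. The plan should be changed because the remedy is cheap, not because an inflated error rate has been shown.

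**What to change.** For the two continuous outcomes, replace the stated model by one of these:

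1. Model the 3- and 9-month values with the baseline value as a covariate, keeping the participant and team random intercepts. Let the baseline slope and the residual variance differ by visit. The separate variance matters for a 9-month contrast under decay. Given baseline, the variances are 1 − 0.837² = 0.30 and 1 − 0.586² = 0.66; pooling them (0.48) would still give about 3.3%. With a 6-month lag, 0.51 and 0.76 pool to 0.635 and give 2.2%. With equal baseline correlations this refinement is not needed.
2. Keep all three visits as responses with an unstructured visit covariance (six parameters) plus the team term, and constrain the arm means to be equal at baseline.

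Without the baseline constraint the two are not equivalent, and baseline adjustment is more precise. At a baseline correlation of 0.5, the averaged contrast has variance 0.85 as a change score and 0.85 − 0.5² = 0.60 after adjustment.

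The text should also name the tested contrast (9 months or the average of both follow-ups). The cost is a sentence or two in the analysis section and one covariate or a few covariance parameters; no new data are needed. The binary outcomes are not covered by this change.
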